### Outcome measures

Outcome measures include the core set of primary efficacy variables recommended by the Outcome Measures in Rheumatology Clinical Trials (OMERACT) group for phase III clinical trials in OA [19] and recommended for inclusion in OA clinical trials by the Cochrane Collaboration [20].

The three *primary efficacy variables*, to be measured at baseline, four, 16 and 26 weeks, are:

• Pain (100 mm VAS and Western Ontario and McMaster Universities Osteoarthritis Index -WOMAC Likert format 3.1). Two measures for pain will be included as this mirrors standard practice in much of the OA literature and it will provide internal validity for this important outcome measure. The reliability of the VAS has previously been demonstrated [21] and is regularly used in this population. WOMAC measures health status and assesses pain, physical function and stiffness in patients with OA of the hip or knee. The WOMAC questionnaire is self-administered and can be completed in less than five minutes. Two major validity studies have shown that WOMAC pain, physical function and stiffness subscales are valid and that the questionnaire is reliable and sensitive enough to detect changes in health status following a variety of interventions [22].

• Patient Global Assessment (100 mm VAS as described by Ehrich et al [23]). Participants are asked to consider all the ways in which their arthritis is affecting them at the time of the assessment and indicate by marking the VAS how they are doing. The left hand anchor of the VAS is *Very Well *while the right hand anchor is *Very Poorly*.

• Physical function (WOMAC Likert format 3.1). Likert values from 17 questions of the WOMAC are summed to generate a score for physical function with a higher score indicating worse function.

#### Secondary outcome measures

• Quality of life (Medical Outcomes Study 36-item Short-Form Survey version 2 – SF-36). The SF-36 has eight sub-component scales reflecting both physical and mental status. It is comprised of 36 questions, is self administered, and can be completed in about 15 minutes. All estimates of score reliability, from 14 separate studies, for each of the eight scales of the SF-36 exceeded accepted standards for measures used in group comparisons [24]. The SF-36 has been extensively validated in many English speaking countries of the world including Australia [25]. The rationale for using both WOMAC and the SF-36 for this trial is that a combined approach using both generic quality of life and knee specific health status measures is considered likely to prove best for knee-related problems [26]. Quality of life measurements will be taken at baseline, four, 16 and 26 weeks.

• Joint stiffness (WOMAC Likert format 3.1) measured at baseline, four, 16 and 26 weeks.

• Global perceived effect scale (GPES) measured using an 11-point scale ranging from -5 (vastly worse) to +5 (completely recovered) with the zero point being unchanged as reported by Pengal et al [27]. This will be measured at 16 and 26 weeks.

• Physical activity will be determined using the HAP questionnaire plus accelerometers measured at baseline and 16 weeks.

◦ The HAP is self-administered. It incorporates 94 activities listed in ascending order of oxygen cost. Respondents are asked to indicate whether they are able to perform the activity unassisted; whether they have ever performed the activity and whether they have stopped performing the activity [28]. In a cross-sectional study, the HAP has been found reliable and sufficiently sensitive for use in people with OA of the knee [29]. This study demonstrated that people with OA of the knee are in fact less active than their healthy counterparts and that there was a relationship between HAP scores and participants' pain and function scores. The proposed trial offers the potential to determine whether improvement in pain and function result in a spontaneous increase in the level of physical activity.

◦ Accelerometry is now considered the preferred method of objectively measuring physical activity as it provides data that allows individual examination of ambulatory activity frequency, intensity and duration [30]. However, to our knowledge accelerometers have not been validated for use in people with OA of the knee. For this trial an Actigraph GT1M (formerly Computer Science and Applications monitor), the most widely accepted accelerometer in research, will be utilised [31]. The match-box size accelerometer will be attached to a belt that the participants will be asked to wear for a period of seven consecutive days at both the baseline and 16 week data collection points.

The benefits of physical activity are well known and include reduced risk of cardiovascular disease, diabetes, some forms of cancer, osteoporosis, falls and fractures. Physical activity interventions have also been shown to assist with weight control and to improve physical functioning and mental health. The impact of physical activity on OA remains unanswered. Osteoarthritis of the knee is often associated with considerable knee pain that suggests that people with knee OA may curtail their physical activity. Although most studies of OA of the knee measure changes in function, few measure physical activity levels so there is limited evidence to demonstrate whether or not this is the case. Moreover whether treatments that reduce pain result in an increase in physical activity is yet to be determined.

### Sample Size Calculations

The primary outcome measure will be defined as an improvement in the absolute pain VAS score of 20. This is the minimum absolute change necessary for classification as a responder in the Osteoarthritis Research Society International (OARSI) response criteria [32,33]. Assuming no change in the placebo group, it has been calculated that a sample size of 70 (35 in each group allowing for 20% withdrawals) will be sufficient to detect this 20 point change as well as differences equal to the absolute minimal clinically important improvements of 19.9 (Pain VAS), 18.3 (PGA) and 9.1 (WOMAC function) described by Tubach et al [34] with a power of 80% using a two-tailed test with alpha level of 0.05. Calculations were based on standard deviations data from Garland et al [11] (Pain VAS and PGA) and Raynauld et al [35] (WOMAC function).

### Statistical Analysis

All analyses will be performed on an intention to treat basis while the investigators remain blind to treatment groups. Change in pain between baseline and 26 weeks will be compared between groups using the independent t-test. To test for the fixed effect of treatment while adjusting for any differences in the baseline measures, repeated measures analysis using a linear mixed model will also be performed for pain VAS, patient global assessment, WOMAC function, stiffness and pain, and QOL measurements taken at four, 16 and 26 weeks. There will be no adjustment for multiple comparisons as all comparisons have been determined a priori and, while adjustment maintains study wise error, it may preclude detection of clinically important differences [36].

Change in activity level between baseline and 16 weeks will also be analysed using the independent t-test. Secondary analyses such as the proportion of participants achieving minimal clinically important improvements in pain, function and patient global assessment at each observation time will be compared using the Chi-square test. GPES at 16 weeks and 26 weeks will be compared between groups using unpaired t-tests.

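### The t-test named first for 26-week pain would, with no imputation stated, use only people with a week-26 value; the mixed model already planned fits the intention-to-treat statement better and should lead.

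*Protocol article*

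**What the plan says.** Statistical Analysis sets one principle for everything: "All analyses will be performed on an intention to treat basis while the investigators remain blind to treatment groups". It then gives two analyses of pain. The first is: "Change in pain between baseline and 26 weeks will be compared between groups using the independent t-test". The second is a baseline-adjusted model on weeks 4, 16 and 26: "repeated measures analysis using a linear mixed model will also be performed for pain VAS", with the other symptom and quality-of-life scores. The article does not say which of the two takes precedence, or how a missing week-26 value enters the t-test.

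Sample Size Calculations ties the trial to pain VAS: "The primary outcome measure will be defined as an improvement in the absolute pain VAS score of 20". It concludes that "a sample size of 70 (35 in each group allowing for 20% withdrawals) will be sufficient to detect this 20 point change", "with a power of 80% using a two-tailed test with alpha level of 0.05".

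The responder proportions, named as secondary analyses, "at each observation time will be compared using the Chi-square test".

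**The concern.** A change score needs both a baseline and a week-26 value. Unless missing values are filled in, a two-group t-test on change drops everyone without the later one, which sits poorly with an intention-to-treat statement that covers every analysis. The article itself allows for 20% withdrawals, so the number affected need not be small.

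Two things are at stake. First, pain is measured at weeks 4 and 16 as well, and the t-test ignores those measurements for anyone who leaves before week 26. Second, people who leave a 26-week symptom trial may differ in outcome from those who stay. If that differs between arms, in how many leave or in which people leave, the comparison among those observed no longer estimates the effect in all randomised. The article already plans a model that handles this better for the same outcome, but introduces it only as something also to be done.

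**Working it through.** **Inputs from the protocol article.** 35 per group, 20% withdrawals, 80% power, two-sided alpha 0.05, 20 mm on pain VAS; pain at baseline and weeks 4, 16 and 26. The t-test sentence says only pain; I take it to mean the VAS, on which the trial is sized. The SD is not printed (only its sources are cited), so N = 70 cannot be reproduced forwards.

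**Step 1: withdrawal arithmetic.** 35 × 0.80 = 28 per group, and 28 / 0.80 = 35. The article's figure is consistent with 28 evaluable per group. An unimputed week-26 t-test at that rate uses 56 of 70 and leaves out 14. The sample size already allows for this, so planned power is not lost. The issue is bias and unused data.

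**Step 2: implied SD.** With 28 per group, 80% power needs a standardised difference of 0.749 (normal approximation, (1.96 + 0.84) × √(2/28)) or 0.762 (t distribution). For 20 mm the SD is 20 / 0.762 = 26.2 to 20 / 0.749 = 26.7 mm. This is back-solved, not a documented value.

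**Step 3: bias of the observed-case difference.** Let m be the fraction missing in an arm, and g the mean improvement of completers minus that of dropouts in the same arm. The completers' mean exceeds the whole arm's mean by m × g, so

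bias = m(active) × g(active) − m(placebo) × g(placebo),

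where a positive value overstates the device. All m and g below are assumptions.

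| Missing, active / placebo | g, active / placebo (mm) | Bias (mm) |
|---|---|---|
| 20% / 20% | 10 / 10 | 0.2×10 − 0.2×10 = 0 |
| 20% / 20% | 10 / 0 | 0.2×10 − 0 = +2 |
| 20% / 20% | 20 / 0 | 0.2×20 − 0 = +4 |
| 10% / 30% | 10 / 10 | 0.1×10 − 0.3×10 = −2 |
| 10% / 30% | 20 / 20 | 0.1×20 − 0.3×20 = −4 |

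**Step 4: an explicit dropout model.** Assume 20% loss per arm. Active losses are random. In the placebo arm the odds of leaving rise by a factor exp(0.5) = 1.6 or exp(1.0) = 2.7 per SD of worse week-26 response. Numerical integration over a normal response gives a shift in the placebo completers' mean of about 2.5 mm for the weaker slope. For the stronger slope it is 4.5 mm at SD 26.2 and 4.6 mm at SD 26.7. Against the target, 2.5/20 = 12.5% and 4.6/20 = 23%. Poor placebo responders are lost, so placebo completers look better and the device's benefit is understated. Equal slopes in both arms give 0.

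**Step 5: what the mixed model recovers.** If dropout depends only on what has been observed (baseline, weeks 4 and 16), a correctly specified likelihood-based model gives a valid contrast. The mechanism in step 4 is harder, because dropout depends on the unseen week-26 value. Predicting week 26 from week 16 then leaves about 1.9 of the 2.5 mm and 3.5 of the 4.5 to 4.6 mm if the two visits correlate at 0.5, and about 1.3 and 2.5 mm at 0.7. Both correlations are assumptions.

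**The case against.** A reader might infer that the primary result is fixed as a completers analysis and so contradicts the intention-to-treat statement outright. The documents do not support that.

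- The article never calls the t-test the primary analysis. It defines a primary outcome measure and names the t-test first; the mixed model covers the same pain VAS.
- It does not limit the t-test to completers. A t-test can be run on imputed values, and an article commonly leaves the missing-data rule to the full protocol or analysis plan.
- Allowing for 20% withdrawals is routine inflation of the sample size. It neither defines an analysis set nor forecasts that 20% of week-26 values will be missing.

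The size is also open to challenge. The larger figures need outcome-related loss in one arm and random loss in the other, and they use a back-solved SD. Skin irritation gives no ground for expecting a difference: the safety section reports similar proportions in the two earlier trials, 17.9–24% active and 21–21.1% placebo. In the modelled scenario the bias runs against the device, and the mixed model removes only part of it.

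All of this stands and limits the strength of the point. It does not remove it. Whatever rule the full documents hold, the article puts first an analysis that, as described, uses less of the data and needs a stronger missing-data assumption than the one it adds afterwards. If the t-test was not meant to lead, two analyses of the main outcome are unranked, and the same wording change settles that.

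**Conclusion.** The point holds as a cheap improvement, not as an essential correction. As described, the 26-week t-test would rest on about 28 of 35 per group at the planned withdrawal rate and would ignore the earlier pain scores of up to 14 people. Its bias is 0 if dropout and its relation to outcome are alike in both arms. It reaches about 4.6 mm (23% of the 20 mm target) in the most unequal scenario examined, and may go in either direction. These sizes rest on an SD of about 26 mm inferred from N = 70 and on assumed dropout patterns; they show what could happen and are not predictions.

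The denominator of the responder chi-square tests, and whether people who stop using the device are still assessed, are related but secondary. The full protocol or analysis plan may settle both, and their absence from the article is not a fault.

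**What to change.** In Statistical Analysis, name the week-26 treatment contrast from the planned baseline-adjusted linear mixed model as the primary analysis of pain VAS, including all randomised participants with at least one post-baseline value (week 4, 16 or 26). Keep the independent t-test on observed change as a sensitivity analysis, and say that it uses only those with a week-26 score.

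The cost is a few lines of wording. The model and the visits are already planned and N stays at 70. The downside is small and should be stated: the model relies on missing at random, does not fully remove bias if dropout depends on the unseen week-26 outcome, and gains nothing from people with no post-baseline value.

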### Randomisation and blinding

An administrator, not otherwise involved with the trial, will allocate the participants to groups using computer-generated block randomisation combined with stratification. Groups will be stratified with regard to gender, age (<60, 60–75 and >75), and intensity of pain (VAS scores 25–40, 41–60 and 61–100). The administrator will dispense an appropriate device using a list, provided by the senior biomedical engineer who modified the devices, that matches the device serial numbers to active or placebo. Participant identification will be added to the list at the time of randomisation so, should the need arise, the investigators will be able to determine the nature of the device provided to a participant without risk of becoming aware of assignment for any other participants (Figure 2). The measurer though will remain blinded to assignment throughout.

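### The pain comparison at 26 weeks is fixed as an unadjusted t-test although randomisation is stratified on baseline pain, gender and age: valid, but it forgoes power that the planned data could give

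*Protocol article*

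**What the plan says.** **Randomisation and blinding** specifies "computer-generated block randomisation combined with stratification". The factors are given as "Groups will be stratified with regard to gender, age (<60, 60–75 and >75), and intensity of pain". The pain factor is the baseline VAS in three bands, so there are 2 × 3 × 3 = 18 strata.

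**Sample Size Calculations** makes pain VAS the sizing outcome: "The primary outcome measure will be defined as an improvement in the absolute pain VAS score of 20". It allows 70 participants (35 per arm with 20% withdrawals), no placebo change, 80% power and two-sided alpha 0.05. The SD is taken from a cited earlier trial and is not printed.

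**Statistical Analysis** lists first: "Change in pain between baseline and 26 weeks will be compared between groups using the independent t-test". It then adds a second analysis: "adjusting for any differences in the baseline measures, repeated measures analysis using a linear mixed model will also be performed for pain VAS" and the other scales, using the visits at weeks 4, 16 and 26. Neither is labelled primary. Activity is handled like pain: "Change in activity level between baseline and 16 weeks will also be analysed using the independent t-test". GPES gets unpaired t-tests and responder proportions get chi-square tests. Gender and age are not named as covariates anywhere in the section.

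**The concern.** A change score does use the baseline, but it fixes the slope on baseline at 1. When the true slope is below 1, change stays correlated with baseline pain. Stratifying on baseline pain balances that variation between the arms, yet an unadjusted t-test still counts it as noise. The standard error is then larger than the real sampling variation of the difference, so the confidence interval is too wide and the test rejects less often than 5% under the null.

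At stake is precision in a trial with about 28 evaluable participants per arm. This matters only if the t-test is what decides the result. The article does not say so, but the t-test is listed first, it matches the two-group sizing calculation, and the mixed model is introduced as an addition. The model is described as a test of the treatment effect over three visits, so as written it does not clearly supply an adjusted answer to the 26-week question.

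**Working it through.** **Inputs from the protocol article:** difference 20 mm, power 80%, two-sided alpha 0.05, 35 per arm, 20% withdrawals, stratification by gender, age band and pain band.

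**Assumed, because the article does not give them:** the correlation r between baseline and week-26 VAS, the block size (4), equal variances at the two visits, withdrawal at random.

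**1. The plan's own figure.** Evaluable per arm: 35 × 0.8 = 28. The sample size cannot be reproduced independently because no SD is printed. Solving backwards with the normal approximation:

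SD = 20 / [(1.960 + 0.842) × √(2/28)] = 20 / 0.749 = 26.7 mm.

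The noncentral t gives 26.2 mm. So the stated 80% holds if the SD of change is about 26 mm.

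**2. Effect of adjusting for baseline.** With a common visit SD σ:

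- variance of change = 2σ²(1 − r)
- residual variance under ANCOVA = σ²(1 − r²)
- ratio = (1 − r²) / [2(1 − r)] = (1 + r)/2

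Adjusted SD = 26.2 × √((1 + r)/2). The detectable difference at 80% power shrinks by the same factor.

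| r | ratio | adjusted SD (mm) | detectable difference (mm) | power at 20 mm | gain over 80% |
|---|---|---|---|---|---|
| 0.2 | 0.60 | 20.3 | 15.5 | 95.1% | 15 |
| 0.3 | 0.65 | 21.1 | 16.1 | 93.5% | 13.5 |
| 0.5 | 0.75 | 22.7 | 17.3 | 89.9% | 10 |
| 0.7 | 0.85 | 24.2 | 18.4 | 86.0% | 6 |
| 0.8 | 0.90 | 24.9 | 19.0 | 84.0% | 4 |
| 0.9 | 0.95 | 25.5 | 19.5 | 82.0% | 2 |

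**3. Simulation with the stratified design.** 70 randomised in blocks of 4 within pain × age × gender, 20% random dropout, 6,000 trials per scenario, ANCOVA on baseline VAS alone.

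| r | type I error, t-test | type I error, ANCOVA | power, t-test | power, ANCOVA |
|---|---|---|---|---|
| 0.3 | 3.1% | 5.5% | 82% | 93% |
| 0.5 | 3.7% | 5.2% | 80% | 89% |
| 0.7 | 4.1% | 5.1% | 80% | 85% |
| 0.8 | 4.7% | 5.1% | 79% | 83% |

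A second simulation, with baseline VAS confined to 25–100 mm, agreed. At r = 0.3, 0.5 and 0.7 the t-test's type I error was 3.0%, 3.3% and 4.4%. Power was 82%, 81% and 79% unadjusted against 93%, 89% and 84% adjusted.

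**4. Limits of the check.** The gain shown comes from baseline pain; what gender and age add cannot be computed from the article. The equal-variance formula with this SD is strained at high r: at r = 0.8 the visit SD would be 26.2/√0.4 = 41.4 mm, above the maximum possible for a score held within 25–100 mm (75/2 = 37.5 mm). Treat that end of the range as a bracket.

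**The case against.** The strongest reply is that the plan already adjusts for baseline. The sentence after the t-test provides a mixed model for pain VAS that does so, and baseline pain VAS is itself one of the stratification factors. A reader might infer that the plan ignores baseline pain altogether. The documents do not support that: the change score uses baseline, and the mixed model adjusts for it. What remains is that the model is not given the deciding role, has no stated week-26 contrast and names neither gender nor age.

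A reader might also infer that the trial is underpowered. That is not shown either. The 26 mm SD was solved to give 80%, and under it the unadjusted test simulates at 79–82%, as promised. A shortfall would appear if the unprinted SD were that of a single visit and r were below 0.5 (t-test power about 66% at r = 0.3), but the article does not say which SD it is.

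Third, a fixed figure of 4 to 10 points is tempting. It holds only for r of about 0.5 to 0.8, and the conservatism fades as r rises.

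Fourth, calling the t-test primary is an inference. It is the natural one, but the text does not state it.

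For responders, 20 mm is 50–80% of entry pain in the 25–40 mm band (20/40 to 20/25) and 20–33% in the 61–100 mm band (20/100 to 20/61). This applies to both arms, and stratification balances the bands between them, so it shows no bias in the chi-square test.

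Exact covariate lists may sit in a fuller document. The choice of an unadjusted t-test, however, is fixed here.

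**Conclusion.** The point holds as a forgone gain of moderate importance. If the unadjusted t-test decides the 26-week pain result, it is valid and errs on the conservative side, so neither bias nor excess false positives follow. Compared with baseline adjustment it gives up about 4 to 10 points of power for a correlation of 0.8 down to 0.5, and 2 to 15 points for 0.9 down to 0.2. These sizes rest on an assumed correlation, equal visit variances and a back-solved change SD of about 26 mm; the type I error figures also rest on assumed blocks of 4. If the mixed model's week-26 contrast were the deciding analysis, most of the loss would disappear. For activity change the same argument applies in principle but is not quantified, and for GPES and responder proportions no gain is shown.

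**What to change.** In Statistical Analysis, name one baseline-adjusted analysis of pain VAS at 26 weeks as primary: either ANCOVA, or the week-26 treatment contrast of the mixed model already planned. Include continuous baseline VAS, gender and age as covariates, and state that the unadjusted t-test is supportive. Adjust activity change at 16 weeks for its own baseline value in the same way. Adjusting GPES and the responder comparisons for baseline pain, gender and age is optional.

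The cost is wording only, to be settled before unblinding. Screening pain VAS, age and gender are all recorded before allocation, and the sample size need not change. The covariates use three or four degrees of freedom out of about 54 (56 evaluable minus 2).

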The second PES trial [11] examined 58 subjects using the same stimulation device in the same manner over 12 weeks. In this trial significant and clinically meaningful results were reported in patient global assessment, a pain and symptom visual analogue scale, WOMAC function and stiffness and overall WOMAC score. Only WOMAC pain change between the placebo and active groups did not reach statistical significance.

No randomised, controlled trials studying this particular modality over a longer time period have been found.

The modality being investigated is neither invasive nor pharmaceutical. As the majority of those with OA of the knee are likely to be elderly, they are also more likely to have co-morbidities such as heart and lung disease which increase the anaesthetic risk associated with invasive surgery. Similarly, there is increasing awareness of the adverse side effects of many of the medications that are used to manage OA of the knee [13-15]. Consequently, in a climate where patients are seeking different options in their disease management strategies, the potential for PES to provide an effective, safe alternative that is acceptable to the community is very high.

This research proposes to investigate the longer term effectiveness of PES and to determine the sustainability of responses in subjects with symptomatic knee OA.

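### The protocol gives two different primary endpoints and no rule for success, and pre-specifying the comparisons does not replace control of study-wise error

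*Protocol article*

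**What the plan says.** Three sections of the protocol article bear on what decides the trial.

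- **Outcome measures** gives a plural primary: "The three *primary efficacy variables*, to be measured at baseline, four, 16 and 26 weeks". The three are pain, patient global assessment (PGA) and WOMAC physical function. Pain is taken on both a 100 mm VAS and the WOMAC subscale ("Two measures for pain will be included as this mirrors standard practice in much of the OA literature"), so there are four measures.
- **Sample Size Calculations** gives a singular primary: "The primary outcome measure will be defined as an improvement in the absolute pain VAS score of 20". The 20 points come from a responder criterion. The same paragraph also claims adequate size for differences of 19.9 (pain VAS), 18.3 (PGA) and 9.1 (WOMAC function), "with a power of 80% using a two-tailed test with alpha level of 0.05".
- **Statistical Analysis** compares change in pain from baseline to 26 weeks by t-test, without naming VAS or WOMAC. It also fits a linear mixed model to pain VAS, PGA, the three WOMAC subscales and quality of life. It lists proportions reaching a minimal important improvement as secondary. On multiplicity it says: "There will be no adjustment for multiple comparisons as all comparisons have been determined a priori". The same sentence accepts that adjustment is what preserves the study-wise error.

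No section ranks the primary variables or says how many must be significant.

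**The concern.** A confirmatory trial should let a reader say beforehand which result counts as success. Here one section gives three primaries and another gives one. The analysis section does not settle the matter, because it labels no test as primary.

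The gap could change the conclusion. The Background reports that in the earlier 12-week trial of the same modality a pain and symptom VAS reached significance, as did most other outcomes, but "Only WOMAC pain change between the placebo and active groups did not reach statistical significance". The choice of pain instrument, which the analysis section leaves unnamed, is the very choice on which that trial's results split.

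The reason given for not adjusting does not answer this. Pre-specification and error control are separate safeguards: four tests fixed in advance, each at 0.05, still give four chances of a false positive. If the plan is instead read as requiring every primary variable to succeed, type I error is not the problem, but the 80% power quoted for each variable is not the power of the trial.

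**Working it through.** **Inputs from the documents.** Two-sided alpha 0.05 and 80% power; 70 participants, "35 in each group allowing for 20% withdrawals"; target differences 20, 18.3 and 9.1; three primary variables on four measures.

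**Inputs not in the documents.** The standard deviations are attributed to cited trials but not printed. Correlations between the measures are not given; I assume a common correlation r between the test statistics, from 0 to 0.8.

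**The plan's own figure.** 35 × (1 − 0.20) = 28 evaluable per arm, so the withdrawal step is consistent. Without SDs the total of 70 can only be back-solved. From SD = difference / [(1.960 + 0.842) × √(2/28)], 80% power holds for SDs up to 26.7 (pain VAS, 20), 24.4 (PGA, 18.3) and 12.2 (WOMAC function, 9.1). No target is given for WOMAC pain.

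**Reading 1: pain VAS at 26 weeks, one test, is the sole primary.** False-positive rate 5%.

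**Reading 2: significance on any primary measure suffices.** For independent tests the rate is 1 − 0.95^k: 1 − 0.95³ = 14.3% for three variables and 1 − 0.95⁴ = 18.5% for four measures. For correlated tests it is the probability that at least one of k equicorrelated standard normal statistics exceeds 1.96 in absolute value.

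**Reading 3: all three variables must succeed.** The false-positive rate is at most 5%. Take each test statistic as normal with mean 1.960 + 0.842 = 2.80, so that each has 80% power. Joint power is the probability that all three exceed 1.96; with independence it is 0.8³ = 51%.

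| Assumed r | Any of 3, false positive | Any of 4, false positive | All of 3, power |
|---|---|---|---|
| 0 | 14.3% | 18.5% | 51% |
| 0.5 | 12.5% | 15.6% | 61% |
| 0.7 | 10.9% | 13.1% | 66% |
| 0.8 | 9.8% | 11.4% | 69% |

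The false-positive columns count results in either direction. Counting only false results in favour of the active device, the rates are about 5% to 7% (three) and 6% to 10% (four), against a nominal 2.5%.

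**T-test or mixed model.** The table counts one analysis per measure. If either analysis of pain VAS alone could carry the claim, a simulation with 28 per arm gives about 8% to 9%. It assumes a correlation of 0.5 between visits and uses a baseline-adjusted mean of the three follow-ups in place of the mixed model.

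**What adjustment would cost.** Bonferroni over three variables (0.0167 each, critical value 2.39) gives power Φ(2.80 − 2.39) = 66%. Over four measures (0.0125 each, critical value 2.50) it gives Φ(2.80 − 2.50) = 62%. A single named primary keeps 80%.

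**The case against.** The strongest defence is that the sample size and analysis sections can be read together as one plan. The calculation uses standard deviations, assumes no change on placebo and seeks a 20-point difference on the VAS. A t-test of mean change in pain at 26 weeks fits that, and the responder proportions are expressly secondary. On this reading the error rate is 5%. The defence also notes that the article declines adjustment openly, with a reason and a citation, and that a separate analysis plan may state a rule for success.

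Much of this stands. A reader might infer three mutually incompatible primary definitions, but the documents support one contradiction (three variables against one) and some loose wording in the other two sections. A reader might also infer that the trial's false-positive rate is 13% to 19% when the protocol promises 5%. That does not follow: the article states no any-of-several rule, the hypothesis joins its outcomes with 'and', no correlations are given, and 5% study-wise error is never claimed. Nor would it be fair to judge the plan by the power of a 20 mm responder test, which the analysis section makes secondary, or by a count of all planned tests, most of which are secondary.

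What the defence does not remove is the list of three primary variables, the unnamed pain instrument and the unranked pair of analyses. Disclosing that adjustment is declined does not make pre-specification a valid reason for it. These are points the article states, not details left to a later document.

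**Conclusion.** The point holds in a limited form. The Outcome measures and Sample Size Calculations sections contradict each other on the primary endpoint. The Statistical Analysis section does not resolve this, because it names neither the pain instrument nor the deciding analysis, and no success rule is given. The stated ground for not adjusting is mistaken.

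The consequence depends on the reading: a two-sided false-positive rate for a primary claim of 5% with pain VAS alone, or about 10% to 19% if any of three or four measures suffices. If all three variables must succeed, joint power is about 51% to 69%. The last two ranges rest on assumed equal correlations between 0 and 0.8, and the power range also assumes exactly 80% power for each variable. Each reading has a defect: the first contradicts the list of three primaries, the second inflates the error rate, and the third has less than 80% power.

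**What to change.** Before any analysis by group:

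1. Name change in pain VAS from baseline to 26 weeks as the single primary endpoint, with one stated analysis (the t-test or the mixed-model contrast at 26 weeks), at two-sided 0.05. Label the other analysis as supportive.
2. Reword Sample Size Calculations so that 20 mm is the planning difference between group means and not the definition of the outcome.
3. Relabel PGA, WOMAC function and WOMAC pain as secondary. Either test them in a stated fixed order after the primary, or report them with 95% confidence intervals as supportive.
4. Delete the justification that comparisons were set in advance. With one primary and ranked secondaries it is not needed.

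The cost is wording. Sample size, alpha and power for the pain VAS test are unchanged. The downside is that claims on the other measures become somewhat harder to make.
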